### Interim analyses {21b}

No interim analyses will be performed in this study.

### Methods for additional analyses (e.g. subgroup analyses) {20b}

Methods for additional analyses will be described in the SAP.

### Methods in analysis to handle protocol non-adherence and any statistical methods to handle missing data {20c}

Missing data and reason for the missingness will be presented. Missing data for the primary endpoint will be imputed with a negative outcome (flare). Comparisons of missing data between treatment groups and robustness analyses including missing data imputation will also be performed according to the SAP.

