**Methods:**

In this investigator-initiated multicenter, randomized, 3-grouped, parallel, open-label, noninferiority trial, treating physicians at seven Norwegian pediatric rheumatology hospital centers will include 150 patients with JIA. Key eligibility criteria are as follows: Fulfilment of the International League of Associations for Rheumatology (ILAR) classification criteria for non-systemic JIA, inactive disease for ≥ 12 months documented at a minimum of 2 consecutive visits, and no active uveitis for ≥ 24 months under treatment with stable doses of MTX and TNFi.

They will be randomized in a 1:1:1 ratio to (A) stable treatment, (B) methotrexate withdrawal, or (C) TNFi withdrawal. Randomization will be stratified for JIA subtype and study center. For patients in group B and C who are still in remission after 12 months, a new randomization will be performed for complete medication withdrawal for the next 12 months. After 24 months, medication adjustments will be done with shared decision-making. The primary endpoint is the rate of disease flare compared between the drug withdrawal groups and the stable treatment group between baseline and 12 months follow-up. The key secondary endpoint is the proportion with disease flare compared between the two withdrawal groups. Incidence and severity of adverse events will be monitored.

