### Sample size {14}

The primary objective is to assess the non-inferiority of each of the drug withdrawal groups B and C to control group A in terms of disease flare (yes/no) during the 12-month follow-up. Due to two primary comparisons, a Bonferroni correction is applied to account for multiple testing, resulting in a significance level of 2.5%. Further, non-inferiority is assessed by comparing the upper bound of the 97.5% confidence interval of the risk difference to the pre-specified 20% non-inferiority margin. Thus, a significance level of 1.25% is used when determining the required sample size.

Available data suggest that the rate of disease flare when continuing stable treatment (group A) is approximately 10%. Due to the non-inferiority set-up, we assume that the risk of disease flare is equal in all three groups. Using a non-inferiority margin of 20%, power of 80%, and significance level of 1.25%, we estimate that randomization of 43 patients per group would be required. Assuming a 15% drop-out rate, a total of 150 participants will be randomized.

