## Statistical methods

### Statistical methods for primary and secondary outcomes {20a}

The sample size was determined by using R-function *ssc_propcomp* (non-inferiority hypothesis) in *SampleSize4ClinicalTrials* -package (R Foundation for Statistical Computin, Vienna, Austria). R or statistical software for data science (STATA) will be used to analyze the results of the study.

The main analyses will be performed according to a predefined Statistical Analysis Plan (SAP) when all participants have concluded the study, all data have been entered, verified, and validated, and the database has been locked. The SAP can be provided upon request to the authors. The intention-to-treat (ITT) set will include all patients randomly assigned to a treatment group irrespective of post-randomization occurrences. The per-protocol analysis set (PPS) will include all randomized patients meeting the study entry criteria who followed the study protocol with no major protocol deviations. The primary analyses will be performed based on the PPS. Due to the non-inferiority setting, a per-protocol approach was chosen to assess the effect among participants who adhered to the protocol to avoid bias toward no treatment difference, thereby reflecting the effect under optimal implementation, while the ITT set will be used for sensitivity analysis. The safety analyses will be performed using the ITT set.

Baseline characteristics will be summarized descriptively by treatment group using mean and standard deviation or median and interquartile range for continuous variables, and counts and percentages for categorical variables.

The primary objective of the trial is to assess the non-inferiority of each of the drug withdrawal groups B and C to control group A. The two primary hypotheses are the following:Group B (withdrawal of MTX, stable TNFi) is non-inferior to group A (stable MTX and TNFi), i.e., the difference between the groups in the proportions of study participants having disease flares during the 12-month follow-up period is less than or equal to the pre-specified non-inferiority margin of 20%.Group C (withdrawal of TNFi, stable MTX) is non-inferior to group A (stable MTX and TNFi).

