As two primary non-inferiority tests are performed simultaneously, a Bonferroni correction will be applied, and primary endpoints tested at the 0.025 level to control the overall probability of Type I error. The non-inferiority of groups B and C to group A will be evaluated by estimating a risk difference and its 97.5% confidence interval from the logistic regression model with disease flare as a binary outcome and treatment group and stratification variables (study site and JIA course (persistent oligoarticular JIA versus other non-systemic JIA categories)) as covariates. The upper bound of this confidence interval will be compared to the non-inferiority margin of 20%. Non-inferiority is claimed if the primary null hypothesis is rejected at the significance level of 0.0125 (one-sided), that is, if the upper limit of the 97.5% two-sided confidence interval for the treatment difference is less than 20%. In case the primary null hypothesis (1) or (2) is not rejected (group B/C is inferior to group A), the superiority of group A to group B/C will be examined (key secondary).

Key secondary objective is to compare the disease flare rates during the first 12 months follow-up in two drug withdrawal groups B and C. The key secondary hypothesis is that the risk of disease flare during the first 12 months of follow-up is equal in arm B (withdrawal of MTX with stable TNFi) and arm C (withdrawal of TNFi with stable MTX). The comparison will be performed as a two-sided superiority test by estimating a risk difference and corresponding 95% confidence interval from the logistic regression model with disease flare as a binary outcome and treatment group and stratification variables (study site and JIA course (persistent oligoarticular JIA versus other non-systemic JIA categories)) as covariates. Based on the results, the direction and the clinical relevance of the difference may be examined.

The results of the trial will be reported according to consolidated standards of reporting trials (CONSORT).

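### Scoring every missing primary outcome as a flare, with no analysis set named, does not fit the drop-out allowance: power is about 55% to 80% depending on who stays in the primary set, and the rule is not reliably conservative for non-inferiority

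*Protocol article*

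**What the plan says.** All references are to the protocol article.

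- **Sample size {14}.** The control rate is given as follows: "Available data suggest that the rate of disease flare when continuing stable treatment (group A) is approximately 10"%. For the other groups, "we assume that the risk of disease flare is equal in all three groups". The number needed per group is stated as follows: "Using a non-inferiority margin of 20%, power of 80%, and significance level of 1.25%, we estimate that randomization of 43 patients per group would be". Drop-out is then added: "Assuming a 15% drop-out rate, a total of 150 participants will be randomized". With 1:1:1 allocation that is 50 per group.
- **Statistical methods for primary and secondary outcomes {20a}.** The per-protocol set is primary. It holds randomized patients who met the entry criteria and had no major protocol deviation. The reason given is to avoid a bias towards finding no difference, "thereby reflecting the effect under optimal implementation, while the ITT set will be used for sensitivity analysis". The text does not say whether leaving before 12 months is a major deviation. The test is defined as follows: "Non-inferiority is claimed if the primary null hypothesis is rejected at the significance level of 0.0125 (one-sided"), using a risk difference from a logistic model.
- **Missing data {20c}.** "Missing data for the primary endpoint will be imputed with a negative outcome (flare"). No analysis set is named. The section then leaves comparisons of missingness between groups and further robustness analyses to the SAP.

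**The concern.** The two sections treat the same patients differently. Going from 43 to 50 per group makes sense if drop-outs leave the denominator and the rest flare at 10%. The rule in {20c} puts patients without an outcome into the numerator as events. If they are in the analysed set, the flare proportion is well above 10%, the variance of the risk difference is larger, and 43 evaluable patients is no longer the right target.

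The second issue is direction. Scoring missing as failure is often taken to be a cautious choice. In a non-inferiority comparison, adding similar shares of events to both arms pulls a true difference towards zero. That is the bias {20a} gives as its reason for choosing the per-protocol set. What is at stake is the chance of a correct non-inferiority claim when withdrawal is harmless, and the chance of a false one when it is not.

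**Working it through.** **Inputs from the article:** flare rate 10% in every group, margin 20 points, one-sided alpha 1.25% (z = 2.2414), power 80% (z = 0.8416), drop-out 15%, 50 per group.

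**Assumptions of this check:** an unadjusted Wald limit stands in for the model-based one. Missingness is unrelated to flare. The shares of missing outcomes are illustrative, because the article gives no rate of missing outcomes overall or by arm.

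**1. The plan's own figure.** n = (2.2414 + 0.8416)² × (2 × 0.10 × 0.90) / 0.20² = 42.8, so 43 per group, as stated. Also 43 × 1.15 = 49.5, so 50 per group and 150 in total. Dividing by 0.85 gives 51 per group (153); this small difference is not the issue here.

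**2. Drop-outs excluded.** 50 × 0.85 = 42.5 per group at 10%. SE = √(0.18/42.5) = 0.0651. Power = Φ(0.20/0.0651 − 2.2414) = 79.7%. The plan is then consistent.

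**3. Missing outcomes kept and scored as flares.** With missing share m, the analysed proportion is p′ = m + (1 − m) × 0.10, and power = Φ(0.20/√(2p′(1 − p′)/50) − 2.2414).

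| m | p′ | SE | Power |
|---|---|---|---|
| 5% | 14.5% | 0.0704 | 72.5% |
| 10% | 19.0% | 0.0785 | 62.1% |
| 15% | 23.5% | 0.0848 | 54.7% |

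Exact binomial enumeration gives 55.2% at 15%. Keeping 80% power at p′ = 23.5% needs 3.083² × (2 × 0.235 × 0.765) / 0.04 = 85.4, so 86 per group.

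**4. Between the two readings.** If 15% drop out without an outcome and only some stay in the per-protocol set, power is 79.7%, 68.8%, 61.9%, 57.5% and 54.7% when 0%, 25%, 50%, 75% and 100% of them stay.

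**5. Direction, equal missingness.** The analysed difference is (1 − m) × (p_B − p_A). Take the boundary case, a true 10% v 30%, with m = 15%. The analysed proportions are 23.5% and 40.5%, a difference of 17 points. Exact probability of claiming non-inferiority, 50 per arm:

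| m, both arms | Apparent difference | Exact type I error |
|---|---|---|
| 0% | 20 points | 1.6% |
| 5% | 19 points | 1.9% |
| 10% | 18 points | 2.3% |
| 15% | 17 points | 2.8% |

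The Wald limit exceeds its nominal 1.25% even with complete data, so 1.6% is the fair baseline.

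**6. Direction, unequal missingness.**
- 20% in A, 10% in the withdrawal group, true 10% v 30%: analysed 28% v 37%, apparent difference 9 points. False-claim probability is 14.4% by the formula and 14.7% exact.
- 10% in A, 20% in the withdrawal group, true 10% v 30%: analysed 19% v 44%, apparent difference 25 points. False-claim probability is about 0.26%.
- The same 10% v 20% missingness with no true difference: analysed 19% v 28%, a spurious 9 points. Power is 17.4% by the formula and 18.1% exact.

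**The case against.** The strongest reply is that the primary set is per-protocol. If leaving early is a major deviation, drop-outs are not in that set, the step from 43 to 50 is coherent, and power is 79.7%. The rule then acts mainly on the ITT sensitivity analysis. This stands as one reading, and it is why a reader who infers that the trial simply has 55% power goes too far. That figure needs all 15% to lack an outcome and all of them to stay in the primary set. The article does not settle the matter either way.

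It is also fair that drop-out is not the same as a missing outcome. Flare is assessed at every scheduled and extra visit, suspected flares are to be seen within two weeks, and leavers are offered a discontinuation visit. A child who flares before leaving has an observed outcome, so the missing share may be below 15%. At 5% missing, power is still only 72.5% if those patients are kept.

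A reader might also infer that the rule always favours withdrawal. It does not. With no true difference and equal missingness there is nothing to shrink, and more missingness in a withdrawal group works against a non-inferiority claim. The trial is open-label, and the introduction says that patients may prefer to stop MTX, but no document gives drop-out by arm. More missingness in group A is possible and not established.

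Finally, {20c} leaves robustness analyses to an SAP that is not shown, so their absence here is no fault. The rule itself, however, is fixed in the article, and additional analyses do not change it.

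**Conclusion.** The point holds in conditional form. The article fixes a missing-data rule without naming the set it acts on, and neither reading works well. If early leavers stay in the primary set, the rule undercuts the stated 80%: with 15% drop-out, power lies between about 55% and 80% according to how many of them stay. If they are excluded, the rule has little to act on in the primary analysis, but it shrinks a true difference in the supporting ITT analysis whenever missingness is similar across arms.

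Power loss and type I inflation are separate problems that arise under different truths. The inflation under equal 15% missingness is moderate (about 1.6% to 2.8%). Under unequal missingness the error can be about 14-15% or about 0.3%, depending on which arm has more. The rule therefore gives no dependable protection in either direction. These sizes rest on the article's design inputs, an unadjusted Wald limit, missingness unrelated to flare, and assumed missing shares.

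**What to change.** 1. In {20a}, state whether patients who leave before 12 months belong to the per-protocol set. In {20c}, state to which set or sets the imputation rule applies.
2. In any set that keeps these patients, base the main estimate on flare data observed up to drop-out. One way is multiple imputation of 12-month flare status by arm, using JIA course, visits attended and last JADAS-27, feeding the logistic risk difference already planned.
3. Add a sensitivity analysis that worsens the imputed outcomes in groups B and C only, since that is the direction that tests a non-inferiority claim.
4. Keep missing = flare as a sensitivity analysis.
5. If the sponsor prefers to keep the rule for the primary analysis, restate the power in {14}: about 55% with 15% missing at 50 per group, or 86 analysed per group for 80%.

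Items 1 to 4 cost protocol and SAP wording and a little programming, with no extra patients. The downside is a missing-at-random assumption in the main estimate, which item 3 probes. The article reports 40 participants included and plans no interim analysis, so the change can be made without knowledge of results by arm.

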### Plans to give access to the full protocol, participant level-data and statistical code {31c}

MOVE-JIA is registered on clinicaltrials.gov and on Clinical Trials in the European Union (CTIS). The full trial protocol (version 1.2, 06.05.2025) and statistical code are available from the corresponding author upon request. At present, data sharing is not applicable.

## Oversight and monitoring

### Composition of the coordinating centre and trial steering committee {5d}

The Department for Rheumatology at Oslo University Hospital (OUH) is the coordinating center for the project. The Pediatric Rheumatology Research Group has performed numerous open studies on disease outcomes and clinical genetic predictors in JIA patients, and a recently completed randomized controlled trial on JIA treatment (the MyJIA trial, ClinicalTrials.gov: NCT04614311). The study has been planned and will be performed in collaboration with the Norwegian Clinical Research Infrastructure Network (NorCrin), the center for treatment of rheumatic and musculoskeletal diseases (REMEDY), and the research group works closely with the Clinical Trial Unit (CTU) at OUH. The CTU offers advising in GCP, data management, monitoring, statistics, and more. A steering committee has been appointed, including two members independent of the study.

### Composition of the data monitoring committee, its role and reporting structure {21a}

There will not be a data monitoring committee for this study.

### Adverse event reporting and harms {22}

Adverse events (AE) will be collected at every study visit from the start of the study until the last follow-up visit. An adverse event will be considered serious (SAE) if it results in any of the following: death, a life-threatening adverse event, in-patient hospitalization or prolongation of hospitalization, disability or permanent damage, or a congenital anomaly/birth defect. All SAEs will be recorded and reported to the sponsor or designee immediately and under no circumstances should this exceed 24 h. If a SAE occurs, the investigator will determine if it is related to the study medication based on clinical judgement. The degree of certainty about the association will be certain, probable, possible, or unlikely. The medical monitor and the trial sponsor will be notified automatically through the eCRF.

### Frequency and plans for auditing trial conduct {23}

The coordinating center will remotely evaluate the quality of trial activities if indicated. In-person site visits with the monitor will be conducted at regular intervals, estimated once yearly during the recruitment period and one visit after the last patient’s last visit. As Oslo University Hospital will recruit the majority of patients, monitoring will be conducted twice a year during the recruitment period at this center.

### Plans for communicating important protocol amendments to relevant parties (e.g. trial participants, ethical committees) {25}

All protocol amendments must be approved by the ethics committee and the Norwegian Medical Products Agency through the CTIS system before all study centers will receive the updated version of the protocol. Regular newsletters will be sent to all study personnel and user representatives.

## Dissemination plans {31a}

Communication of results from the trial will be based on peer-reviewed publications, websites, and in collaboration with user societies. Multiple abstracts will be submitted to national and international congresses.

## Discussion

The MOVE-JIA trial is the first randomized controlled trial comparing stable combination therapy with MTX and TNFi to treatment withdrawal strategies for children and adolescents with JIA in remission. While there is limited evidence on the effect of discontinuing therapy, tapering or withdrawing medications is common practice in pediatric rheumatology. This trial aims to address this knowledge gap and provide much-needed evidence to guide treatment decisions. The results from the trial will directly translate into evidence-based clinical decision making for JIA patients with sustained inactive disease. All potential outcomes of the study may influence clinical practice and treatment recommendations and guidelines.

The main objective is to determine if the drug withdrawal groups are non-inferior to stable treatment with TNFi and MTX in children and adolescents with JIA in sustained inactive disease, i.e., if withdrawal of MTX and stable treatment with TNFi is non-inferior to stable combination therapy, and if stable treatment with MTX and withdrawal of TNFi is non-inferior to stable combination treatment. Should either of the treatment withdrawal strategies demonstrate non-inferiority, this would have important implications for clinical practice with a shift in mode/pattern and extent of treatment tapering in more patients. Key secondary objective is to assess the risk of disease flares between the two different withdrawal strategies. Should TNFi monotherapy prove non-inferior to continued combination therapy and superior to MTX monotherapy, this could support simplifying long-term treatment to TNFi alone, potentially reducing the burden of care and side effects for patients. Such evidence would inform updated treatment guidelines and support more personalized treatment decisions based on individual tolerability.

In addition to flare rates, the study will provide valuable insights into the ability to regain remission following a disease flare. Understanding how readily patients can achieve inactive disease after a flare, and how long this takes, will help clinicians balance the benefits of tapering with the potential risks. The study will also explore the risk of developing anti-drug antibodies in patients undergoing treatment changes, and the possibility of achieving drug-free remission, a long-term goal for many patients and caregivers. The results may contribute to better evidence-based information for shared decision-making, ultimately improving long-term health, functional outcomes, educational and work participation, and quality of life for young people with JIA. Importantly, the results may extend beyond JIA and be transferable to other inflammatory diseases in children, such as inflammatory bowel disease, uveitis, psoriasis, and connective tissue diseases using the same combination therapy.

While the study is designed to reflect real-world clinical practice, some limitations should be acknowledged. A potential risk is the challenge of recruiting a sufficient number of eligible participants, particularly given the relatively low prevalence of patients with JIA in sustained remission on combination therapy. To address this, the trial is designed as a multicenter study to maximize reach and ensure a broad and diverse participant pool. If recruitment targets are not met as planned, the primary study center will increase its recruitment efforts, and additional centers may be invited to join the trial. This flexible recruitment strategy is intended to ensure that the study achieves its target sample size and maintains statistical power. Additionally, the generalizability of the results may be influenced by differences in healthcare systems and access to biologic therapies. Also, as with all pragmatic clinical trials, there may be challenges related to treatment adherence and follow-up.

Nevertheless, the MOVE-JIA trial is expected to generate high-quality, clinically relevant data that will form a scientific basis for optimized long-term JIA management and inform future treatment recommendations. By identifying the most effective and well-tolerated approach to maintenance treatment, all outcomes from the trial will provide a scientific basis for optimized JIA care and more evidence-based treatment recommendations.

